# Implantable collamer lens implantation (ICL) versus small incision lenticule extraction (SMILE) in low to moderate myopia: study protocol for a randomized, non-inferiority trial

**DOI:** 10.1186/s13063-022-06851-3

**Published:** 2022-10-28

**Keywords:** Myopia, Refractive surgery, Implantable collamer lens implantation, Small incision lenticule extraction

## Abstract

**Background:**

Implantable collamer lens implantation (ICL) is a form of ‘foldable’ posterior chamber phakic intraocular lens refractive surgery that generally does not impair cornea and natural accommodation. The potential advantages of the ICL over keratorefractive laser procedures include less induction of higher-order aberrations (HOAs) and enhanced retinal image magnification. On the other hand, small incision lenticule extraction (SMILE), currently, one of the most popular refractive surgery procedures, also offers excellent visual outcomes, particularly for eyes with low to moderate amounts of myopia. The aim of this study is to evaluate whether ICL/TICL (toric ICL) is comparable to SMILE for low to moderate myopia in terms of refractive outcomes at 3 and 18 months post-operatively.

**Methods/design:**

This is a prospective randomized study. A total of 300 participants will be randomized into two groups, the ICL/TICL group and SMILE group. Eligible participants with spherical equivalent (SE) less than − 6.0 diopter (D) will be recruited. Following randomization, participants will be followed at 1, 3, 6, 12, and 18 months. The primary outcome is the refractive predictability at every postoperative point after surgery, which is the proportion of the number of eyes achieving a postoperative SE within ± 0.5 D and ± 1.0 D of the intended target. Secondary outcome parameters include visual acuity, refraction, adverse events, and quality of vision measurements.

**Discussion:**

This trial will provide information on whether ICL has comparable, if not superior, refractive outcomes compared to the established SMILE for low to moderate myopia, thus providing evidence for translation into clinical practice.

**Trial registration:**

Chinese clinical trial registry (ChiCTR) 2200055372. Registered on 08 January 2022.

## Background

Myopia, a common form of refractive error, is a leading cause of visual impairment and has been successfully corrected with refractive surgery globally [1, 2]. As refractive surgery has evolved beyond traditional laser procedures alone over the past decade, a broader surgical selection is now available, including now phakic intraocular lens [2, 3]. Currently, small incision lenticule extraction (SMILE), a form of refractive surgery, has become a popular laser refractive surgery and offers good visual outcomes, less iatrogenic dry eye, and good safety profile [4, 5]. Characterized by flapless and minimally invasive technique, SMILE has the potential for better corneal biomechanical stability [6], larger functional optical zones [7], and fewer surgically induced corneal higher-order aberrations (HOAs) [8].

The EVO Visian Implantable Collamer Lens (V4c ICL; STAAR Surgical, Monrovia, CA, USA), a posterior chamber phakic intraocular lens which incorporates CentraFLOW technology, has become widely accepted as a long-term effective approach for myopia correction, especially in the high range of myopia [9–11]. The potential advantages of the ICL over keratorefractive laser procedures include higher contrast sensitivity, higher retinal image magnification, and less induction of higher-order aberrations (HOAs) [11–13]. However, since ICL still has a potential complication related to endothelial cell loss, aqueous flare, and crystalline lens transmittance decreased in short term [14], the efficacy of ICL for low- to moderate-range myopia has not been demonstrated.

Although ICL is rapidly gaining popularity in many parts of Asia and the European Union, the number of ICL cases is still far fewer than excimer laser refractive procedures, especially in myopia with less than 6.0 diopters (D). Our previous clinical outcomes already indicated that ICL can offer acceptable safety, predictability, and stability for high myopia [15], and some comparative studies between keratorefractive laser surgery and ICL implantation for correction of high myopia concordantly showed superior refractive accuracy and subjective visual quality for the latter technique [12, 13, 16]. However, there are currently few randomized controlled trials comparing between ICL and SMILE in low to moderate myopia.

Non-inferiority trials are used to compare the standard procedure with a relatively new treatment which is expected to have some advantages such as greater predictability, safety, efficacy, and less side effects [17, 18]. SMILE was considered as the current standard refractive surgery for low to moderate myopia [2, 4] and produced good visual outcomes with refractive predictability [5]. As we do not expect to see a great improvement to the results from the already established SMILE, we aim to demonstrate that ICL is just as good in terms of visual outcome in this randomized non-inferiority trial for the low to moderate range of myopia.

## Methods/design

### Study design and randomization

This is a prospective, randomized controlled trial performed at Xi’An AIER eye hospital. The study adheres to the tenets of the Declaration of Helsinki and is registered at the Chinese clinical trial registry (ChiCTR2200055372) and used the SPIRIT reporting guidelines [19]. It was approved by the Xi’An AIER eye hospital ethics committee (AIER-Xian-2018001). Inclusion and exclusion criteria are shown in Table 1. Randomization will be performed on the day of surgery using a web-based, online, sealed envelope-based system (https://www.sealedenvelope.com). Specific study information sheets will be provided to patients prior to taking consent. Following a dedicated screening and randomization visit for eligible patients, participants will be randomized to one of two trial arms (Fig. 1) and then followed for 18 months at 1, 3, 6, 12, and 18 months (Fig. 2). Face-to-face adherence reminder sessions will take place at the initial trial and subsequent sessions will occur at the follow-up visits. To enhance adherence, simple strategies will be used including mobile phone or WeChat reminder service for participants at follow-up time. Because of the nature of the intervention, surgeon and participant masking will not be possible, so follow-up measurements will be performed by masked optometrists. The retreatment (secondary surgery) for refractive regression will not be permitted for all participants during the trial. However, after 18 months, retreatment must be performed for patients after refraction is stabilized. This protocol is the second version and is revised on Jan 2022. Recruitment commenced on May 2018, and the follow-up of the last recruited patient will be estimated to complete on Dec 2022.

**Table 1 Tab1:** Inclusion and exclusion criteria for trial participants

**Inclusion criteria**	21 years of age or older
	Spherical equivalent of ≤ -6.00 D
	Refractive cylinder ≤ -2.00 D
	Best spectacle-corrected visual acuity (BCVA) of 20/40 or better
	Spherical or cylindrical error has progressed at − 0.50 D or less per year before the baseline measurement
	Contact lens must have been removed at least 2 weeks before the baseline measurement
	No evidence of irregular astigmatism on corneal tomography
	Anterior chamber depth ≥ 2.8 mm
	Corneal endothelial cell count ≥ 2000/mm^2^
**Exclusion criteria**	Progressive or unstable myopia and/or astigmatism
	Clinical or corneal topographic evidence of keratoconus
	Residual, recurrent or active ocular disease and retinal disease
	Previous corneal surgery
	Taking systemic medications and systemically immunocompromised or systemic disease likely to affect wound healing, such as diabetes, connective tissue disease, and severe atopy; pregnant or nursing

**Fig. 1 Fig1:**
[figure not shown]
The comparing trial Consolidated Standards of Reporting Trials (CONSORT) flow diagram

**Fig. 2 Fig2:**
[figure not shown]
The schedule of enrolment, interventions, and assessments of this trial (SPIRIT figure)

### Baseline assessment

At baseline all patients were assessed as follows:Visual acuity (unaided and corrected), Snellen Chart at a starting distance of 6 m (m) in both eyes.Subjective refraction, both eyes.Corneal tomography and corneal center thickness, Scheimpflug imaging (Pentacam) in both eyes.High-order aberration, ray-trace imaging (iTrace) in both eyes.

### Surgical interventions

#### ICL/TICL procedure

In the ICL/TICL group, ICL power calculation is performed by the manufacturer in all cases using the proprietary online form (https://evo-ocos.staarag.ch; version 4.08). ICL/TICL size was selected based on anterior chamber depth (Pentacam) and horizontal corneal diameter (Pentacam). After cycloplegia and topical anesthesia are administered, a model V4c ICL/TICL is inserted through a 2.8-mm clear corneal incision at the steepest meridian and the remaining ophthalmic viscosurgical device is completely washed out of the anterior chamber with a balanced salt solution. Postoperatively, nonsteroidal anti-inflammatory drugs (Pranoprofen; Pranopulin, Senju) and antibiotic medications (Levofloxacin; Cravit, Santen) are administered topically 4 times daily for 2 weeks, and the dose is steadily reduced thereafter.

#### SMILE procedure

In the SMILE group, the VisuMax 500-kHz femtosecond laser (Visumax, Carl Zeiss Meditec AG) is used to create the femtosecond laser dissection planes for SMILE. The spot distance is 3 mm for lamellar cuts and 2 mm for side cuts. The spot energy is set to 140 to 150 nJ. The minimum lenticule side-cut thickness is set to 10 mm. The cap diameter is 7.5 mm with a 2.5-mm side-cut and a side-cut angle of 90°. After surgery, patients receive levofloxacin 0.5% eyedrops (Cravit; Santen, Osaka, Japan) and dexamethasone 0.1% eyedrops (Maxidex; Alcon-Couvreur, Puurs, Belgium) 4 times daily for 2 weeks. Artificial tears (HYCOSAN 0.1%; URSAPHARM Arzneimittel GmbH, Saarbrücken, Germany) are prescribed after surgery, and the dosage is adjusted based on the patients’ symptoms.

### Outcomes and trial duration

All patients are assessed at baseline, 1, 3, 6, 12, and 18 months. We plan to use standard primary and secondary outcomes measures at 3 months postoperatively, which is reported as standard outcomes in refractive studies. The primary outcome is the refractive predictability at each time point after surgery, which is the proportion of the number of eyes achieving a postoperative spherical equivalent (SE) within ± 0.5 D and ± 1.0 D of the intended target [5]. Secondary outcomes included.Unaided visual acuity (UDVA) and best corrected visual acuity (CDVA) following surgery in the study eye using the Snellen chart at a starting distance of 6 m.Refraction (measured dioptric spherical equivalent, myopia, and astigmatism).Refractive astigmatism measured by refraction and corneal astigmatism based on the keratometry readings from the Pentacam corneal topography.Quality of vision as assessed by ocular high-order aberrations (HOAs) using the iTrace system.Changes in corneal endothelial cell count, intraocular pressure, and lens vault.

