### Sample size

As this is a non-inferiority trial with a binary outcome, we have calculated the required sample size using the maximum likelihood method for a large sample [20]. A review of the current literature reveals that the reported refractive predictabilities in ICL and SMILE range from 90.0% [12] to 97% [15] and from 93% [4] to 99% [5], respectively. We therefore assumed the refractive predictabilities in ICL and SMILE in this study are 95% and 97%, respectively. Thus, a sample size of 200 subjects (400 eyes) was deemed to be sufficient to confirm non-inferiority with a power of ≥ 80% and at a 5% significance level using a 2% non-inferiority margin, which is the clinically significant difference from our preliminary data. To account for a lost to follow-up rate of 30%, 300 subjects will be recruited instead of 200. Patients will be recruited for this trial through two primary mechanisms: local advertising and research patient database. Local advertising takes advantage of the audio-visual media as well as internet social platform. The Xi’an AIER refractive error patient registry (database) has been maintained since 2017 and currently contains more than ten thousand patients (more than 12 million people now live in the city).

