### Data collection

Patients were first involved in this research at a patient event hosted by Xi’an AIER Eye Hospital. Topics on which opinions were collected included randomization, cross-over, and the duration of follow-up of trial patients. The staff members from Xi’an AIER Eye Hospital refractive center were responsible for generating the allocation sequence and enrolling participants. The trained research nurses, supervised by the surgeon, will obtain written consent from participants in the trial. The investigators will communicate a summary of the trial results to participants. The burden of the intervention was discussed at our initial meeting with patients and at the consent-taking stage in the trial. All patients will have data collection forms outlining the schedule of each follow-up visit and data to be collected at each visit, which include visual acuity, refraction results, clinical examination, and other outcome measures as described above. According to our previous experience and strategies for adherence, few patients will discontinue or deviate from the protocol. However, participants may withdraw from the study for any reason at any time. The primary and secondary outcomes will be collected from patients discontinued from the study at the last follow-up visit. Furthermore, the effect that any missing data might have on results will be assessed via sensitivity analysis. Dropouts (participants who non-adherence or discontinue from the protocol) will be included in the analysis by modern imputation methods for missing data. All data access and trial conduct will be monitored by the supervisors ([name] and [name]). An interim analysis will be performed on the primary endpoint when 50% of patients have been randomized and have completed the 3 months follow-up. The interim analysis will be performed by an independent statistician who is blinded for the treatment allocation. The statistician will report to the AIER central ethics committee (ACEC). The ACEC will have access to all data and will discuss the results of the interim analysis. The ACEC will decide on the continuation or stopping of the trial according to interim-analysis results. At the end of the study, the research data will be entered by the research assistant and stored for up to 3 years in compliance with any integrity issues that may arise from any subsequent publications. Following that time period, the data will be kept under the control of the supervisor. The technical appendix, statistical code, and dataset are available from the Dryad repository, https://doi.org/10.5061/dryad.0vt4b8h1g.

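### The primary endpoint is not identified: its visit is stated inconsistently and its two refractive windows are unranked, so the error rate of the non-inferiority claim cannot be determined

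*Protocol article*

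**What the plan says.** Statements about the visit:

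- Protocol article, Outcomes and trial duration, one sentence: "We plan to use standard primary and secondary outcomes measures at 3 months postoperatively".
- Same section, next sentence: "The primary outcome is the refractive predictability at each time point after surgery".
- Abstract, Methods/design: "The primary outcome is the refractive predictability at every postoperative point after surgery".
- Abstract, Background, in the study aim: "in terms of refractive outcomes at 3 and 18 months post-operatively".
- The visits are fixed: "All patients are assessed at baseline, 1, 3, 6, 12, and 18 months".

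Statements about the window: predictability is the proportion of eyes "within ± 0.5 D and ± 1.0 D of the intended target". The abstract gives the same pair. Neither place says which window is primary.

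The sections that depend on the primary endpoint treat it as a single quantity:

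- Sample size uses one pair of rates (ICL 95%, SMILE 97%), without a window or visit, "at a 5% significance level using a 2% non-inferiority margin".
- Data collection says "An interim analysis will be performed on the primary endpoint when 50% of patients have been randomized" and have completed 3-month follow-up.
- Statistical analyses gives one rule: non-inferiority is confirmed if the upper 90% confidence limit for SMILE minus ICL does not exceed 2%. It names no window or visit and does not say whether one, any or all results must satisfy the rule.

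**The concern.** A non-inferiority conclusion has a known error rate only if the comparison that decides it is fixed. Here the two sentences that should fix it disagree about the visit, and nothing chooses between the windows. The statement that non-inferiority is confirmed therefore corresponds to no single test.

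Three things are at stake. The chance of a false claim depends on an unstated rule. The interim analysis, which can lead to the trial being stopped, refers to an endpoint that is not identified. And the two windows are not equally demanding: the wider one is easier to pass under the same 2-point margin, so leaving the window open leaves the stringency of the test open.

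**Working it through.** **Inputs from the protocol.** Five postoperative visits (1, 3, 6, 12, 18 months), two windows, a 2-point margin, and the upper limit of a 90% confidence interval, which is a one-sided 5% test.

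**Assumptions.** 1:1 allocation, which is not stated. Equal correlation between all test statistics, shown over a range because the protocol gives no value.

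**1. Does the planned sample size reveal the endpoint?** The assumed difference is 97% − 95% = 2 points, which equals the margin. Power is then 5% at any sample size, so the stated 200 participants (400 eyes) cannot be reproduced. Equal rates of 97% would need 900 eyes per arm. That is a separate problem. It matters here only because the figure cannot be traced back to a particular window or visit.

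**2. Number of candidate comparisons.** 5 visits × 2 windows = 10.

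**3. Any one may carry the claim, every true difference at the margin.** With independent tests the false-claim rate is 1 − 0.95^k:

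- k = 10: 1 − 0.95^10 = 0.401
- k = 5: 1 − 0.95^5 = 0.226
- k = 2: 1 − 0.95² = 0.0975

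With equicorrelated normal test statistics:

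| Candidates | Corr. 0.9 | Corr. 0.7 | Corr. 0.5 | Independent |
|---|---|---|---|---|
| 10 (all visits, both windows) | 0.12 | 0.19 | 0.25 | 0.40 |
| 5 (all visits, one window) | 0.09 | 0.14 | 0.17 | 0.23 |
| 2 (one visit, both windows) | 0.07 | 0.08 | 0.09 | 0.10 |

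**4. All ten must pass.** A false claim then requires every test to pass, including at least one whose null hypothesis is true, so error is at most 5%. The cost is power. If each test alone had 80% power (an illustration, not a property of this trial), the joint power would be 0.38 at correlation 0.5, 0.57 at 0.8 and 0.64 at 0.9.

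**5. The two windows.** Every eye within 0.5 D is also within 1.0 D, so the 1.0 D rate cannot be lower. Take 200 eyes per arm (400 eyes, 1:1), equal true rates p, and eyes treated as independent, so SE = √(2p(1 − p)/200).

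- p = 97%: SE = √(2 × 0.0291/200) = 0.0171. The one-sided half-width is 1.645 × 0.0171 = 2.8 points, so an observed difference of zero would fail. Power is Φ(0.02/0.0171 − 1.645) = 0.32.
- p = 99.5% (an assumed rate, not in the protocol): SE = √(2 × 0.004975/200) = 0.00705. The half-width is 1.2 points, so an observed difference of zero would pass. Power is Φ(0.02/0.00705 − 1.645) = 0.88.

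Correlation between the two eyes would lower both power figures. Also, if both true rates are at least 98%, they cannot differ by more than 2 points, so the margin excludes nothing.

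**The case against.** **The 3-month sentence settles the visit.** There is support for this. The interim analysis also pairs the primary endpoint with 3-month follow-up, and the 3-and-18-month phrase states an aim rather than defining the primary outcome, so it should not be counted as a third definition. But the next sentence and the abstract both say every visit. Even if 3 months is accepted, two windows remain, with 7% to 10% error if either may carry the claim.

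**The analysis plan will order the tests.** Multiplicity handling is commonly left to that document, and its absence here is not the finding. The finding is that the protocol's own definition of its primary outcome conflicts with itself, which an analysis plan would have to resolve rather than merely elaborate.

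**A reader might infer that the trial runs ten tests and claims success on any of them, at 40% error.** The text does not say so. It describes one interval, one margin and a singular endpoint. Ten is a count of possible readings. The 40% figure also requires independence, which is implausible for nested windows and repeated visits on the same eyes.

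**A reader might take the high pass rate in the 1.0 D window as false non-inferiority.** It is not. With equal true rates, passing is the correct conclusion, so the figure is power under an assumed rate. If the 1.0 D differences truly lie within the margin, those five tests add no false claims. The relevant inflation is then that of the five 0.5 D tests, about 9% to 17% at correlations of 0.9 to 0.5.

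**A reader might infer that the endpoint was left open or changed after results were seen.** Last follow-up in December 2022, less 18 months, puts the last surgery near June 2021, so 3-month visits probably ended before the January 2022 revision. This is circumstantial. Nothing shows that the revision touched the outcome or that comparative results had been seen, and the protocol places data entry at the end of the study. The dates justify asking for disclosure and no more.

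**Conclusion.** The point stands as an internal contradiction about the visit together with an undesignated window. As written, the error rate of the main claim is not determinable. It ranges from at most 5%, with a large loss of power, if all ten comparisons must pass, to about 12% to 25% if any one suffices. The upper range rests on three assumptions: an any-pass rule that the protocol does not state, every true difference at the margin, and equal correlations between 0.5 and 0.9. The wider window discriminates less under the same 2-point margin. That direction follows from the nesting of the windows, while its size depends on rates the protocol does not give. It should be corrected before analysis, because the trial's principal conclusion depends on it.

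**What to change.** - **Designate one primary endpoint, by window and visit.** If version 1 of the protocol fixed one specifically, keep it and say so. Otherwise use the proportion of eyes within 0.5 D of target at 3 months, the visit that the outcomes section calls standard and that the interim analysis already uses.
- **Disclose timing.** State when the choice was made relative to access to outcome data. Designating an endpoint now is itself a late choice, so this statement is needed for it to be credible.
- **Demote the rest.** Treat the other window and visits as secondary or supportive, not as alternative routes to the primary claim.
- **Use one label throughout.** Put the same window and visit in the abstract's methods, Outcomes and trial duration, Sample size (where the 95% and 97% rates need labelling), the interim analysis text in Data collection, and Statistical analyses. Align the aim in the abstract's background.

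The cost is wording in those places and giving up the option to choose among results. No additional participants, visits or measurements are needed.
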